## Abstract

**Background:**

"Use it or lose it" is a well known saying which is applicable to boys with Duchenne Muscular Dystrophy (DMD). Besides the direct effects of the muscular dystrophy, the increasing effort to perform activities, the fear of falling and the use of personal aids indirectly impair leg and arm functions as a result of disuse. Physical training could oppose this secondary physical deterioration. The No Use is Disuse (NUD) study is the first study in human subjects with DMD that will examine whether a low-intensity physical training is beneficial in terms of preservation of muscle endurance and functional abilities. The study consists of two training intervention studies: study 1 "Dynamic leg and arm training for ambulant and recently wheelchair-dependent boys with DMD and, study 2 "Functional training with arm support for boys with DMD who have been confined to a wheelchair for several years". This paper describes the hypotheses and methods of the NUD study.

**Methods:**

Study 1 is an explorative randomized controlled trial with multiple baseline measurements. Thirty boys with a DNA-established diagnosis of DMD will be included. The intervention consists of a six-months physical training during which boys train their legs and arms with active and/or assisted cycling training equipment. The primary study outcomes are muscle endurance and functional abilities, assessed with a Six-Minute Bicycle Test and the Motor Function Measure. Study 2 has a within-group repeated measurements design and will include ten boys with DMD who have already been confined to a wheelchair for several years. The six-months physical training program consists of 1) a computer-assisted training and 2) a functional training with an arm support. The primary study outcome is functional abilities of the upper extremity, assessed with the Action Research Arm Test.

**Discussion:**

The NUD study will fill part of the gap in the current knowledge about the possible effects of training in boys with DMD and will increase insight into what type of exercise should be recommended to boys with DMD. The study will finish at the end of 2010 and results are expected in 2011.

**Trial registration:**

The Netherlands National Trial Register1631

## Background

Duchenne Muscular Dystrophy (DMD) is an inherited X chromosome-linked recessive myopathy which affects approximately 1/4200 live-born boys[1]. DMD is characterized by a total, or near-total (<3%), absence of the cell membrane protein dystrophin. The absence of dystrophin results in a steady degradation of muscle fibers that causes progressive loss of muscle strength and functional abilities[2,3]. Boys with DMD are usually confined to a wheelchair at the age of ten years[4] and have a median life expectancy of thirty years with spinal surgery and assisted ventilation[5]. Although ongoing studies show promising therapies that target disease cause, there is still no curative (pharmaco)therapy available and, thus, treatment remains symptomatic. An important aim in the management of boys with DMD is to preserve functional abilities for as long as possible[6]. Delaying the loss of functional abilities is relevant for all activities in daily life and may optimize independence in boys with DMD.

The loss of functional abilities is primarily the result of a progressive decrease in muscle strength and muscle endurance during the course of the disease[4,7]However, increasingly limited physical and social possibilities gradually cause a secondary reduction of physical activity. Indeed, the increasing amount of energy a certain activity costs, the increasing frequency of falling (with the need for help to stand up), and the developing fear of falling further reduce leg and arm activities, resulting in disuse of the musculoskeletal and cardiorespiratory systems[8]. The use of an electrical wheelchair limits arm functions (like reaching and lifting) even more, since a top blade and a central operating joy stick force boys to function within the confines of the wheelchair. As the increased sedentary lifestyle results in progressive disuse, secondary physical deterioration will occur in all boys with DMD. Disuse in DMD thus can be defined as the discrepancy between a boy's potential capacity and his actual performance. To underscore the importance of disuse, previous studies have shown that the presence of hip, knee and elbow flexion contractures is strongly related to the onset of wheelchair dependence[4]. Another example is that boys with DMD have a higher risk of bone fractures due to osteoporosis caused by unloading[9]. Fractures as a result of falling are followed by a loss of ambulation in 20-40 percent of the cases[10,11]. In these aspects, the well-known saying "use it or lose it" is certainly applicable to boys with DMD.

Physical training could oppose the secondary deterioration of muscle tissue and the loss of functional abilities as a result of disuse. However, the number of studies that examined the effects of training in DMD is limited, and only a few training studies are reported in human subjects with DMD. These studies focused on resisted exercises in ambulatory boys and concluded that sub-maximal resistance exercises had only limited positive effects on muscle strength and timed functional tests (such as the time it takes to walk 23 feet) but, importantly, they did not cause physical deterioration[12-14]. Recent studies in mdx mice (an animal model for DMD) concluded that voluntary wheel running (dynamic training) had positive effects on muscle strength[15] and fatigue resistance[15-17]. In addition, non-weight bearing low-intensity exercises (like swimming) had no detrimental effects in mdx mice[18]. However, extrapolating data from animal studies to humans should only be done with great caution because of differences in phenotypic expression and biomechanical differences between humans subjects and animal models with muscular dystrophy[19]. Based on the currently available evidence, and clinical experience, international guidelines recommend ambulatory boys to perform voluntary (eventually mechanically-assisted) active exercises (such as swimming) and to avoid eccentric exercises. Non-ambulant boys are advised to perform mobilizing passive or actively-assisted mobilizing exercises to maintain postural symmetry and sitting comfort[20].

The mechanisms by which training may oppose the deterioration of muscle tissue is unclear. Muscle fibres in DMD are abnormally vulnerable to contraction-induced injury due to the absence of mechanical reinforcement of the sarcolemmal membrane[21]. Therefore, eccentric exercises should be avoided[22]. On the other hand, work-induced damage can enhance muscle regeneration and repair[23], and low-stress exercise may produce beneficial effects on myofiber contractility and energetic efficiency[21]. For example, low-intensity training decreased oxidative stress markers[24] and caused a shift from fast-twitch muscle fiber type 2 to slow-twitch muscle fiber type 1 in mdx mice[16]. Slow-twitch muscle fibers are more resistant to muscle fiber degeneration[16,25]. In addition, corticosteroids could support the beneficial effect of training in DMD, since steroids may prevent post-exercise deterioration of skeletal muscle[22].

The currently recommended voluntary exercises to maintain comfort and symmetry[6] are widely used in daily practice and assume that low-intensity training is beneficial and not harmful for boys with DMD. However, these recommendations are mainly based on theory and there is a need for more research to justify these recommendations and to define the optimal exercise programmes[26]. As we expect that a low-intensity training may slow-down the secondary decline of muscle endurance and functional abilities (figure 1), we developed the *No Use is Disuse *(NUD) study protocol to answer the clinically relevant questions whether low-intensity physical training in boys with DMD is beneficial and does not cause further harm. The NUD study is the first to examine the effects of low-intensity physical training in human subject with DMD and will fill part of the gap in current knowledge about the possible effects of training in boys with DMD. The study consists of two training intervention studies: study 1 "Dynamic leg and arm training for ambulant and recently wheelchair-dependent boys with DMD and, study 2 "Functional training with arm support for boys with DMD who have been confined to a wheelchair already for several years". This paper describes the hypothesis and methods of the NUD study.

**Figure 1 F1:**
[figure not shown]
Hypotheses

## Methods

### Study 1 Dynamic leg and arm training

#### Design

Study 1 is an explorative randomized controlled trial with multiple baseline measurements. Randomization is stratified according to the ambulatory status (ambulant/non-ambulant) of the boys and the boys are allocated to the intervention group or the control group in a 2:1 ratio. The intervention group receives dynamic exercise treatment, whereas the control group receives usual care (no specific intervention) during 24 weeks. After this period, the control group will also receive the physical training. Randomization is performed by an independent statistician. Despite randomization, differences in baseline characteristics between the intervention group and the control group may still be present due to the relatively small number of participants. For this reason, multiple baseline measurements are performed that will allow us to do within-subject analyses as well. Assessments are not blinded, because it was considered virtually impossible to prevent the boys from revealing their group allocation to the assessor.

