#### Sample size

The average rate of decline (mean and standard deviation (SD)) of muscle endurance and functional abilities in boys with DMD, as assessed with bicycle ergometry and the Motor Function Measure (MFM), is unknown. Therefore, no sample size can be calculated for these primary outcomes. However, it is anticipated that multiple baseline measurements will increase the chance of finding statistically significant changes in the selected outcome measures. For reasons of convenience, and because this RCT should be regarded as a first explorative study, we decided to include 20 boys in the intervention group and 10 boys in the control group.

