#### Analysis

A two-way analysis of variance (ANOVA) will be used to examine the effects of dynamic leg and arm training on the primary outcomes. Secondary outcomes will be treated similarly or by non-parametric analyses dependent on the type of outcome (interval or ordinal). Data will be analyzed with SPSS version 16.0 and an alpha level of 0.05 will be used to decide on statistical significance.

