#### Analysis

A one-way analysis of variance (ANOVA) of time will be used to examine the effects of functional arm training with arm support on the primary outcome (ARAT). Secondary outcomes will be treated similarly or by non-parametric analyses dependent on the type of outcome (interval or ordinal). Data will be analyzed with SPSS version 16.0 and an alpha level of 0.05 will be used to decide on statistical significance.

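### Study 1 stratifies randomisation by ambulatory status, but the two-way ANOVA, most naturally group by time, does not include it; the test is conservative if status predicts the analysed quantity

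*Protocol article*

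**What the plan says.** The Design section of Study 1 in the Protocol article states that "Randomization is stratified according to the ambulatory status (ambulant/non-ambulant) of the boys" and that "the boys are allocated to the intervention group or the control group in a 2:1 ratio". The Sample size section fixes the numbers: "we decided to include 20 boys in the intervention group and 10 boys in the control group". It gives no effect size or SD, because the rate of decline on both primary outcomes "is unknown. Therefore, no sample size can be calculated for these primary outcomes".

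The Analysis section of Study 1 reads: "A two-way analysis of variance (ANOVA) will be used to examine the effects of dynamic leg and arm training on the primary outcomes". It names neither factor and does not mention ambulatory status. The significance rule is that "an alpha level of 0.05 will be used to decide on statistical significance".

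Two other places bear on what the two factors are. The Analysis section of Study 2 says "A one-way analysis of variance (ANOVA) of time will be used", so the one-group study has time as its single factor. The Design section of Study 1 adds that "multiple baseline measurements are performed that will allow us to do within-subject analyses as well", and the Study outcomes section schedules assessments from T0 onwards in both groups.

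**The concern.** Stratified allocation balances the arms on ambulatory status, so differences between ambulant and non-ambulant boys contribute little to the true sampling variance of the treatment effect. The analysis gets credit for this only if its error term also excludes those differences. If the stratum is not in the model, they stay in the residual, and the standard error describes a less precise trial than the one that was run.

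Ambulatory status may well be prognostic here. It is the only stratification factor, Table 1 defines the two subgroups by different functional criteria, and Table 2 reports that the total MFM score predicts loss of ambulation. The trial has 30 boys, 10 of them controls, with the size chosen for convenience, so avoidable loss of power matters.

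**Working it through.** **Inputs from the Protocol article.** 20 intervention and 10 control boys (20 + 10 = 30, ratio 2:1), two strata, alpha 0.05. There is no power calculation to reproduce.

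**Assumptions not in the article.** Two-sided test; 15 boys per stratum (10 intervention and 5 control in each); SD of 1 within group and stratum for the analysed quantity; a stratum gap of g SD in that quantity.

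**Step 1: which factors?** Study 2 has one group and a one-way ANOVA of time. Study 1 has two groups, repeated assessments and a two-way ANOVA. Adding group to time is the natural reading. It is an inference, since the factors are not named.

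**Step 2: true precision.** With exact 2:1 balance within strata, the stratum gap cancels from the difference in means, whether or not the model contains the stratum:

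SE(true) = √(1/20 + 1/10) = √0.15 = 0.387 SD.

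**Step 3: what the unadjusted model reports.** Its residual has 30 − 2 = 28 degrees of freedom and also carries the between-stratum sum of squares, 30 × ½ × ½ × g² = 7.5g². The expected residual variance is therefore 1 + 7.5g²/28, and the SE is inflated by about √(1 + 7.5g²/28):

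| Gap g (SD) | Residual variance | SE inflation |
|---|---|---|
| 0 | 1.000 | none |
| 0.5 | 1.067 | √1.067 = 1.03 |
| 1 | 1.268 | √1.268 = 1.13 |
| 2 | 2.071 | √2.071 = 1.44 |

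Equal strata are the worst case. With 24 and 6 boys, the multiplier falls to 30 × 0.8 × 0.2 = 4.8, and a 1 SD gap gives √(1 + 4.8/28) = 1.08.

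**Step 4: level or change?** In a group-by-time test the treatment effect lies in the change, so g must be a gap in change. Simulation of change scores (20,000 runs per setting, SD of change 1) confirms this:

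| Level gap | Change gap | SE without stratum | SE with stratum |
|---|---|---|---|
| 3 | 0 | 0.384 | 0.384 |
| 3 | 0.5 | 0.396 | 0.384 |
| 3 | 1 | 0.433 | 0.384 |
| 3 | 2 | 0.554 | 0.384 |

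The ratios are 0.396/0.384 = 1.03, 0.433/0.384 = 1.13 and 0.554/0.384 = 1.44, as in Step 3. A large but constant level gap costs nothing.

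**Step 5: effect on the test.** A second simulation (20,000 runs per setting, assumed effect 1.15 SD) sets the stratum's share of outcome variance, R². The matching gap is g = 2√(R²/(1 − R²)).

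| R² | g | Type I error without stratum | Power without stratum |
|---|---|---|---|
| 0 | 0 | 5.2% | 81% |
| 0.10 | 0.67 | 3.7% | 79% |
| 0.25 | 1.15 | 2.5% | 72% |
| 0.50 | 2.00 | 0.5% | 52% |

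With the stratum in the model, type I error is about 5% and power about 81–82% in every row.

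**Step 6: does the estimate suffer?** Under stratified allocation its true SD stays at 0.38–0.39 in every row, even when the model omits the stratum. Under unstratified allocation it would be 0.450 at R² = 0.25 and 0.554 at R² = 0.50.

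**The case against.** Three objections carry weight.

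First, the article never says that ambulatory status is excluded. A reader might infer that the factor is definitely left out, but the text names no factors, and group by ambulatory status also fits the words. The article is condensed, and model terms are often left to an analysis plan. This stands as a limit on certainty. It does not remove the point: a two-way model has room for two factors, and group by ambulatory status would drop time from a design built around repeated measurements.

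Second, a reader might infer that standard errors are too large because ambulant and non-ambulant boys obviously differ in leg cycling and MFM score. That is a difference in level. In a group-by-time test a constant level difference drops out, and loss arises only if the strata change at different rates over 24 weeks. The article offers no evidence of that and says the rate of decline is unknown. This stands, and makes the point conditional.

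Third, the error is on the safe side: it causes no bias and no excess of false positives, in a trial described as explorative. This also stands.

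A further tempting inference is that the balance gained by stratifying is wasted. Step 6 of the working shows that it is not.

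**Conclusion.** The point holds conditionally. On the most natural reading, the planned primary analysis omits the factor by which the boys were randomised. If that factor predicts the analysed quantity, the reported standard error is too large and the test conservative: by about 3%, 13% or 44% for assumed gaps of 0.5, 1 or 2 SD, and not at all if there is no gap.

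These figures rest on an assumed equal split between strata and on assumed gaps; the article supplies neither, so the actual loss cannot be determined from it. The treatment estimate keeps its protection against imbalance in ambulatory status. Only the credit for that precision in the standard error and p-value is at stake. The change is still worth making, because it costs almost nothing when the stratum turns out to be uninformative.

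**What to change.** Name the two ANOVA factors, and include ambulatory status as randomised in the analysis of both primary outcomes in a way that acts on the tested effect. Either of these would do:

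- an ANCOVA of the 24-week value (or change) with group, baseline value and stratum; or
- a repeated-measures model with group, time and group by time, plus stratum and stratum by time.

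In the repeated-measures model a stratum main effect alone is not enough, because it leaves the group-by-time test unchanged.

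For the bicycle test, Table 2 lists T0, T2 and T5 rather than T4, so the visit that supplies the end-of-period value has to be settled first.

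The cost is about one degree of freedom (28 to 27 in the simple comparison) and no new data. A stratified rank test (van Elteren) for the ordinal secondary outcomes would be consistent with this but is optional.

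### Study 1 offers within-subject analyses as the answer to chance baseline differences and never says that the randomised comparison decides whether training works

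*Protocol article*

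**What the plan says.** All references are to the protocol article, Methods, Study 1.

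- **Design.** Randomisation is 2:1 in favour of training, stratified by ambulatory status. Controls have usual care for 24 weeks and then train. The section warns that, with so few boys, the arms could still be unlike at the start. It responds as follows: "For this reason, multiple baseline measurements are performed that will allow us to do within-subject analyses as well". It also says that the assessor is not blinded.
- **Sample size.** With no known rate of decline or SD, the section offers no power calculation and sets 20 trained boys and 10 controls as a convenience choice. Its hope rests on the repeated baselines: "it is anticipated that multiple baseline measurements will increase the chance of finding statistically significant changes in the selected outcome measures". It does not say whether these are changes within boys or differences between arms.
- **Analysis.** The method for both primary outcomes takes one sentence: "A two-way analysis of variance (ANOVA) will be used to examine the effects of dynamic leg and arm training on the primary outcomes". Significance is judged at 0.05. The section names neither the two factors nor the term that decides, and it does not mention the within-subject analyses.
- **Table 2.** As printed, the Six-Minute Bicycle Test, one of the two primary outcomes, is assessed at T0, T2 and T5. The randomised period ends at T4.

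**The concern.** The reason given for the within-subject analyses does not fit the problem. Chance imbalance is a feature of the comparison between arms, and it is handled inside that comparison by adjusting for the baseline values. A before-after analysis of trained boys sets the control arm aside. It tests whether those boys changed, not whether training changed them.

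The distinction matters here because zero is not the expected change without training. The Background describes progressive loss of strength and function. The bicycle test asks for maximal effort and is repeated, so practice is plausible. The assessor knows the allocation. The aim stated in the Background is to slow decline, so a fully successful training could leave trained boys unchanged. A within-subject test would then show nothing while the randomised contrast showed the benefit.

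Because the text does not say that the randomised comparison decides, a reader of the results could meet two conflicting p-values, both judged at 0.05, with no rule for which one answers the question. With 20 and 10 boys the randomised contrast reaches 80% power only for a difference of about 1.1 SD. A non-significant randomised result is therefore quite possible, and that is when a within-subject result is most tempting as a substitute.

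**Working it through.** **The plan's own figure.** There is no power calculation to reproduce. Only the split can be checked: 30 × 2/3 = 20 and 30 × 1/3 = 10, as stated.

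**Inputs.** From the documents: 20 trained boys, 10 controls, alpha 0.05. Assumed: two-sided tests, normally distributed changes from baseline to the end of the 24 weeks, no training effect, and a drift d common to both arms, in SDs of within-boy change. The documents give no value for d, so it is ranged. Positive d means improvement (for example practice) and negative d means decline.

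**Within-subject test in the trained arm.** One form is a one-sample t-test on change, with 19 degrees of freedom and critical value 2.093. Its noncentrality is d × √20:
- d = 0.25: 0.25 × 4.472 = 1.118
- d = 0.50: 0.50 × 4.472 = 2.236
- d = 0.75: 0.75 × 4.472 = 3.354

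**Randomised test.** This is a two-sample t-test on change, 20 v 10. A common d cancels in the difference, so the rejection rate stays at 5% whatever d is.

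| Common drift d (size) | Within-subject test, trained boys | Randomised contrast | Either significant (simulated) |
|---|---|---|---|
| 0 | 5.0% | about 5% | 8.8% |
| 0.25 | 18.6% | about 5% | 22% |
| 0.50 | 56.5% | about 5% | 59% |
| 0.75 | 88.9% | about 5% | 90% |

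**Direction.** The table counts results in both directions. Under improving drift nearly all within-subject rejections point to benefit. Under decline nearly all point to harm. Counting benefit only, at d = −0.25, −0.5 and −0.75, the chance that either test shows a false benefit is about 2.5% (2.4% to 2.7% in simulation). That is what the randomised test alone gives.

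**Masked benefit.** Suppose decline without training is 0.75 SD and training halts it completely. Mean change in trained boys is then 0, and the within-subject test rejects 5% of the time. The randomised contrast has noncentrality 0.75 / √(1/20 + 1/10) = 0.75 / 0.387 = 1.94 on 28 degrees of freedom, which gives 46% power.

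**Another within-subject form.** A contrast of baseline slope (T0 to T2) with training slope (T2 to T4) was simulated with an assumed independent error at each visit. It rejects about 5% of the time under steady linear decline. Under an assumed practice effect that levels off, of 0.5 to 1 error SD, it rejects 18% to 54% of the time.

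**The case against.** The strongest reply is that only one primary analysis is named. The Analysis section assigns the two-way ANOVA to the primary outcomes and places the 0.05 level beside it. The within-subject analyses appear only in Design, in permissive and additive wording. A reader might infer that the protocol sets up two equal routes to a positive result, or fixes a one-sample before-after test. It does neither. The ANOVA may well be meant as group by time. Within-subject analyses could also compare baseline with training slopes, or use the controls' later training period. The rates tabulated above belong to one possible form.

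A reader might also infer that natural decline could be declared a training benefit. The figures do not support that: under decline, false benefit stays near 2.5%. Only improving drift, from practice or unblinded assessment, inflates false benefit, and the documents give no size for it. Nor does the Sample size wording on significant changes necessarily mean within-group change, since averaging repeated baselines also sharpens a between-group contrast.

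Finally, the trial calls itself explorative, and the standing of supplementary analyses is often left to a fuller document. That lowers the weight of the point. It does not remove it, because the objection is to a stated rationale: Design offers within-subject analysis as the response to imbalance, which it does not correct. Ranking the analyses elsewhere would leave that rationale in place.

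**Conclusion.** The point holds as a matter of a misplaced rationale and a missing ranking. Within-subject analyses are presented as the response to chance baseline differences, and no section says that the randomised comparison decides. If a before-after test in the 20 trained boys were taken as the answer, it would be significant 19% to 89% of the time with no training effect, for an assumed common drift of 0.25 to 0.75 SD of change. The randomised contrast stays at about 5%. Improving drift would give false benefit. Decline would give false harm or conceal a real slowing.

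These sizes rest on the assumed drift, on normal changes and on the simple before-after form. Slope-based analyses, or analyses that use the controls' later training, would behave differently. The protocol does not commit to the faulty form, but nothing in it prevents that form from being used as the answer. The point should be addressed, and doing so is cheap.

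**What to change.** 1. First reconcile the Table 2 schedule for the Six-Minute Bicycle Test (T0, T2, T5) with the T4 end of the randomised period. As printed, this primary outcome has no T4 value. T5 falls 4 weeks after training ends in the intervention arm but 12 weeks into training in the control arm, so it cannot serve as the randomised endpoint.
2. In Design and in Analysis, state that the between-group difference over the randomised 24-week period is the deciding test for each primary outcome. It can be the group-by-time term, or the end-of-period value adjusted for the mean of the available baseline measurements.
3. In Design, replace the present reasoning with the statement that this adjustment handles chance baseline differences.
4. Label the within-subject analyses supportive, and say that they do not stand in for the randomised contrast when that is not significant. Whether they carry p-values is a matter of preference.
5. In Sample size, refer to the between-group difference in change.

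The analysis wording costs a few sentences. Reconciling the schedule is a text correction if the test is already done at T4; if it is not, an added assessment would be needed. The downside is that a within-subject change alone can no longer be presented as evidence of efficacy.
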